### Data collection

Data will be collected using an electronic data collection notebook (eDCN) designed for the study. There are four visits planned: enrolment (-t1) baseline (t1), at 6 months (t2) and at 12 months (t3) of the end of the intervention. The flowchart according to SPIRIT guidelines can be seen in Table 1.

### Analysis strategy

Analyses will compare the intervention group (IG) and the control group (CG) and corresponding changes in frailty status, physical performance, cognitive level, mood, and chronic pain between baseline, and three post-intervention points (0, 6, and 12-month post-intervention). Baseline characteristics will be described according to qualitative or quantitative variables: description and analysis of the distribution of each variable, normality tests (Kolmogorov-Smirnov) and scatter charts. Participant attrition will be described in detail. A baseline comparison will be made between the groups: in terms of descriptive, outcome, and prognostic variables. The appropriate bivariate statistical tests will be used according to type of variable (qualitative or quantitative).

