### Sample size

We calculated the sample size based on two data points: the published figure of 15% of pre-frail individuals that transition to robust status in the absence of an intervention [12] and our 35% estimated percentage of pre-frail elderly in the intervention group becoming robust again. Therefore, we expect a difference of 20% of favorable evolution (from pre-frail to robust) between both control and intervention groups. Considering a power of 80% and an alpha of 0.05, the sample size would be 146 patients (73 patients in the intervention group and 73 patients in the control group). Assuming an attrition of 30%, the final number needed to recruit is 190 patients (*n* = 95 in IG and *n* = 95 in CG).

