#### Randomization

Patients will be randomized into IG or CG after completion of baseline data collection (t1) in an automated process included in the Electronic Data Collection Notebook (eDCN).

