### Main analysis of effectiveness

Data will be analyzed using intention-to-treat analyses.

A positive event for the main outcome variable, intervention effectiveness, will be defined as the transition from pre-frailty (1 or 2 Fried criteria) to robust status (zero Fried criteria) during the study period. The accumulated incidence in each group, the relative risk (RR), the number-needed-to-treat (NNT) will be calculated, with their corresponding 95% confidence intervals. We will perform the analysis with the statistical programs SPSS v.24.

Outcome evaluation (changes in frailty) and statistical analyses will be conducted by skilled study staff blind to treatment allocation.

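### SPPB, cognition and mood are described as changes from baseline with no baseline adjustment stated; if compared unadjusted, the plan loses precision and lets chance baseline imbalance shift the result

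*Protocol article*

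**What the plan says.** The only description of how secondary outcomes will be compared between arms is the opening sentence of Analysis strategy in the protocol article. It refers to "corresponding changes in frailty status, physical performance, cognitive level, mood, and chronic pain between baseline, and three post-intervention points", and gives those points as 0, 6 and 12 months. No model or covariate is named for any secondary outcome.

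The same section plans a check of the arms at entry: "A baseline comparison will be made between the groups: in terms of descriptive, outcome, and prognostic variables". The next sentence reads "The appropriate bivariate statistical tests will be used according to type of variable (qualitative or quantitative" and closes the section.

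Table 1 marks a baseline measurement for SPPB, cognitive state (MEC-30), mood (Yesavage), quality of life, blood pressure and BMI. It marks no time point for chronic pain and no baseline for the analytical parameters. The Randomization section states: "Patients will be randomized into IG or CG after completion of baseline data collection (t1", so the baseline values precede allocation.

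The primary outcome is handled separately under Main analysis of effectiveness. It is a binary event, the "transition from pre-frailty (1 or 2 Fried criteria) to robust status (zero Fried criteria", summarized by cumulative incidence, RR and NNT.

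**The concern.** An unadjusted comparison of changes subtracts the whole baseline value from the follow-up value. When the two correlate imperfectly, that over-corrects: the arm that happens to start worse tends to show more improvement through regression to the mean. ANCOVA estimates how much of the baseline to subtract, which removes this effect and gives a smaller residual variance.

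At stake are the secondary objectives on function, cognition and mood. The sample size was set for the binary primary outcome alone, so the precision available for these scales is whatever the analysis extracts from the patients recruited. The planned baseline comparison adds a practical difficulty. It will look for differences between arms in the outcome variables, but the article does not say what happens if one is found. Committing in advance to baseline adjustment makes that question unnecessary.

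**Working it through.** **The plan's own figure.** No sample size or precision is stated for any continuous outcome. The one stated calculation is for the primary outcome: "the published figure of 15% of pre-frail individuals that transition to robust status in the absence of an intervention" and "our 35% estimated percentage of pre-frail elderly in the intervention group becoming robust again", with "Considering a power of 80% and an alpha of 0.05". Using the pooled-variance formula, two-sided:

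n = [1.96·√(2·0.25·0.75) + 0.8416·√(0.15·0.85 + 0.35·0.65)]² / 0.20² = (1.200 + 0.501)² / 0.04 ≈ 72.4, so 73 per arm and 146 in total.

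The stated figure reproduces and plays no part in the point below.

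**Inputs for the check.** 190 recruited and 30% attrition (Sample size section) leave 190 × 0.70 = 133 completers, about 66 per arm. The correlation r and the SDs are not given. I assume r from 0.3 to 0.9, the same r in both arms, and equal SDs at baseline and follow-up, and I work in SD units.

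**Formulas.**
- Residual variance per patient: 2(1−r) for change and 1−r² for ANCOVA. The ratio is 2(1−r)/[(1−r)(1+r)] = 2/(1+r).
- Number of ANCOVA patients to which 133 patients analysed by change are equivalent: 133·(1+r)/2.
- Detectable difference at 80% power, two-sided 0.05, 66 per arm: (1.96 + 0.8416)·√(2/66) = 0.488, times √(2(1−r)) for change or √(1−r²) for ANCOVA.
- Shift in the expected change contrast for a baseline difference b between arms: −(1−r)·b, shown for b = 0.2.

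| r (assumed) | Variance, change | Variance, ANCOVA | Ratio | Equivalent n of 133 | Detectable, change | Detectable, ANCOVA | Shift for b = 0.2 |
|---|---|---|---|---|---|---|---|
| 0.3 | 1.40 | 0.91 | 1.54 | 86 | 0.58 | 0.47 | −0.14 |
| 0.5 | 1.00 | 0.75 | 1.33 | 100 | 0.49 | 0.42 | −0.10 |
| 0.7 | 0.60 | 0.51 | 1.18 | 113 | 0.38 | 0.35 | −0.06 |
| 0.9 | 0.20 | 0.19 | 1.05 | 126 | 0.22 | 0.21 | −0.02 |

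A baseline difference of 0.2 SD is not unusual: with 66 per arm the SD of the chance difference is √(2/66) = 0.17.

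**If the SDs are unequal.** With baseline SD s₀ and follow-up SD s₁, the change variance is s₀² + s₁² − 2r·s₀·s₁ and the ANCOVA variance is s₁²(1−r²). The excess is (s₀ − r·s₁)², which is never negative. The sizes in the table would move, but the direction would not.

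**The case against.** The strongest reply is that the article does not fix an unadjusted change-score test. Its sentence is an overview of what is compared and when. Change can itself be modelled with baseline as a covariate, and that gives the same treatment estimate as ANCOVA on the follow-up value. Covariates for secondary outcomes are commonly left to the statistical analysis plan, which is not shown. This stands, and it is why the loss is stated conditionally. It does not remove the point: the text goes beyond silence by naming change as the quantity compared, and a plain reading gives no hint of adjustment.

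A reader might infer from the bivariate-test sentence that adjusted analysis is ruled out. The document does not support that. The sentence directly follows the one on the baseline comparison and most naturally refers to it.

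A reader might also apply the point to everything in the quoted list, which would be wrong. Frailty status is a binary outcome with everyone pre-frail at entry, and chronic pain has no baseline marked in Table 1. Conversely, quality of life, blood pressure and BMI are not in that sentence, so the article cannot be said to compare them as changes. They enter only the recommendation, because their baseline values exist.

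Finally, the gain is small when r is high, as it may be for some of these measures. That also stands.

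**Conclusion.** The point holds in a limited form. For SPPB, cognition and mood the article names change from baseline as the comparison and states no baseline adjustment, although the pre-randomization values are collected. If the changes are compared unadjusted, the variance is between 5% (r = 0.9) and 54% (r = 0.3) larger than it need be. At r = 0.5 the excess is 33%, so 133 completers do the work of about 100. A chance imbalance of 0.2 SD would shift the contrast by 0.02 to 0.14 SD over the same range. These sizes depend on assumed correlations and equal SDs.

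The stronger conclusion, that the secondary results would be biased, does not follow: allocation is random and the change comparison is unbiased on average. The cost is precision, and dependence on whatever imbalance happens to occur, in secondary outcomes only. The primary analysis and the sample size are unaffected.

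**What to change.** Add a sentence to Analysis strategy. For each continuous secondary outcome with a baseline value in Table 1 (SPPB, MEC-30, mood score, and likewise EQ-5D-5L, blood pressure and BMI), the arm difference is estimated by ANCOVA of the follow-up value on arm and baseline value. Where there is more than one post-baseline visit, a mixed model with baseline as covariate and an arm-by-visit term may be used instead. EQ-5D-5L has a single post-baseline visit in Table 1, so ANCOVA applies there. Present changes from baseline descriptively, and state that the adjustment is made whatever the baseline comparison shows. Leave the binary primary outcome and chronic pain outside this rule.

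The cost is one sentence. No extra patients or measurements are needed, and SPSS v.24, the software named in the article, fits both models. If baseline adjustment was already intended, the sentence simply makes it explicit.

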### Main analysis of effectiveness

Data will be analyzed using intention-to-treat analyses.

A positive event for the main outcome variable, intervention effectiveness, will be defined as the transition from pre-frailty (1 or 2 Fried criteria) to robust status (zero Fried criteria) during the study period. The accumulated incidence in each group, the relative risk (RR), the number-needed-to-treat (NNT) will be calculated, with their corresponding 95% confidence intervals. We will perform the analysis with the statistical programs SPSS v.24.

Outcome evaluation (changes in frailty) and statistical analyses will be conducted by skilled study staff blind to treatment allocation.

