## Abstract

**Background:**

Physical activity may reverse frailty in the elderly, but we encounter barriers to the implementation of exercise programs in this population. Our main aim is to evaluate the effect of a multicomponent physical activity program, versus regular medical practice, on reverting pre-frailty status among the elderly, 12 months post-intervention.

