**Methods:**

Randomized parallel group multicenter clinical trial located in primary care setting, among non-dependent and pre-frail patients > 70 years old, including 190 patients (95 intervention, 95 control group). Intervention: Multicomponent physical activity program (MEFAP, for its acronym in Spanish) with twelve 1.5 h-weekly sessions comprised of: 1. Informative session; 2. Exercises for improving aerobic resistance, muscle strength, propioception-balance and flexibility; and 3. Handing out of at-home exercise chart (twice/week). Main variable: pre-frailty according to the Fried phenotype. Secondary variables: sociodemographic, clinical and functional variables; exercise program adherence, patient satisfaction with the program and quality of life. We will perform an intention-to-treat analysis by comparing the retrogression from pre-frailty (1 or 2 Fried criteria) to robust status (0 Fried criteria) by the end of the intervention, 6 months and 12 months post-intervention. The accumulated incidence in each group will be calculated, as well as the relative risk (RR) and the number needed to treat (NNT) with their corresponding 95% confidence intervals. Protocol was approved by the Ethics Committee Hospital la Paz.

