## Aims

Main goal of the MEFAP-project is to evaluate the effect of a multicomponent physical activity program in the primary care setting, versus regular medical practice, in reversing pre-frailty status [4] 12 months post-intervention among patients over 70 years of age.

Secondary Objectives of the study are:

-To evaluate the effect of MEFAP versus regular medical practice at 0- and 6-months post-intervention regarding: pre-frailty status according to the Fried scale, quality of life, and clinical parameters such as blood pressure, body mass index (BMI), cognitive status, mood and chronic pain, and biological parameters such as metabolic and inflammatory markers.

- Assess adherence to MEFAP and participant satisfaction.

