### Study variables

a) Main Outcome: Change in patient’s frailty level from pre-frail to robust. Frailty status is based on Fried criteria [4]: low gait when walking 4 m, grip strength with the dominant hand measured with a dynamometer, unintentional weight loss > 5% of body weight in the past year, low energy (CES-D) [34], and low physical activity (Yale scale) [35]. Pre-frailty is defined as meeting 1 or 2 Fried criteria and robust status is defined as meeting none (0) of Fried criteria.

b) Secondary outcome variables: Variables related to physical functioning: short physical performance battery (SPPB) [30], risk of falls (measured according to consensus proposal on the prevention of frailty and falls [29]. Quality of life: Measure with the EuroQol questionnaire 5D-5 L [36]. Adherence to the program and degree of satisfaction: Patients will be considered to have a good MEFAP adherence when they have attended at least 75% of the sessions**.** With regard to satisfaction, the dimensions of communication, professional attitude, technical competence and accessibility will be evaluated based on a questionnaire created for this purpose and measured with a Likert scale.

Clinical parameters: blood pressure, BMI, Cognitive state (MEC30 Lobo) [33] mood (Yesavage test) [37], chronic pain, and any chronic drugs consumed in the last two weeks. Analytical parameters: blood count, glucose and glycated hemoglobin, lipid profile, iron metabolism (iron, ferritin, transferrin), vitamin D, vitamin B12, folic acid, total proteins, and albumin and inflammation markers (ESR, CRP and fibrinogen).

c) Independent variables. Sociodemographic**:** age, sex, educational level, economic level (monthly family income in euros), main professional occupation. Clinical: Fracture in the previous five years (specify if hip fracture), Comorbidity or diagnosis of at least 2 diseases from the following list: Heart disease (arrhythmia, heart failure or ischemic heart disease), cerebrovascular disease, diabetes mellitus, chronic lung disease (asthma, COPD or respiratory failure), chronic kidney disease, cancer, and osteoarthritis / limiting arthritis (i.e., affecting activities of daily living).

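### The main-analysis event definition is not tied to the 12-month visit that the main aim names, so the primary RR and NNT can count recoveries that are lost by 12 months

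*Protocol article*

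**What the plan says.** All references are to the Protocol article.

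- **Main aim.** The abstract (Background) asks about the effect "on reverting pre-frailty status among the elderly, 12 months post-intervention". The Aims section repeats the time point: "in reversing pre-frailty status [4] 12 months post-intervention among patients over 70 years of age".
- **Secondary objective.** The Aims section places the earlier time points here: "To evaluate the effect of MEFAP versus regular medical practice at 0- and 6-months post-intervention regarding: pre-frailty status according to the Fried scale".
- **Main outcome.** Study variables describes a change in "frailty level from pre-frail to robust", with no time point.
- **Main analysis of effectiveness.** The positive event "will be defined as the transition from pre-frailty (1 or 2 Fried criteria) to robust status (zero Fried criteria) during the study period". The summary follows: "The accumulated incidence in each group, the relative risk (RR), the number-needed-to-treat (NNT) will be calculated", with 95% confidence intervals.
- **Comparisons over time.** The abstract (Methods) compares reversal "by the end of the intervention, 6 months and 12 months post-intervention". Analysis strategy lists the same three points. Neither of these two sentences marks one point as primary.
- **Visits.** Data collection and Table 1 schedule frailty assessment after baseline at 6 months (t2) and 12 months (t3).
- **Sample size.** The planning rates are 15% (control) and 35% (intervention). No time horizon is given for either.

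**The concern.** The aim concerns status at one time point. The event rule concerns a transition within a period, and accumulated incidence is the usual summary of a first event over such a period. For an irreversible event the two would agree. Fried status moves in both directions, and the article's own Background section calls frailty reversible, so here they can differ.

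The programme lasts 12 weekly sessions and the main aim looks a full year beyond it. Whether the benefit lasts is therefore central to the primary question, and a rule that credits any recovery within the period cannot answer it. The headline RR and NNT could then show a benefit, or a diluted one, that does not reflect the 12-month difference. The wording also leaves room to choose between two definitions once the data are seen.

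**Working it through.** **1. The definitions side by side, for a patient who is pre-frail at baseline**

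| t2 (6 months) | t3 (12 months) | Main aim | Main-analysis rule, read naturally |
|---|---|---|---|
| robust | robust | success | success |
| not robust | robust | success | success |
| robust | not robust | failure | success |
| not robust | not robust | failure | failure |

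The two differ only in the third row. The question is how much that row can matter.

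**2. The plan's own figure**

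Inputs from Sample size: p1 = 0.15, p2 = 0.35, power 80%, alpha 0.05 (taken as two-sided). With mean rate 0.25, the pooled-variance formula without continuity correction is

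n = [1.96·√(2·0.25·0.75) + 0.842·√(0.15·0.85 + 0.35·0.65)]² / 0.20² = 72.4, so 73 per arm and 146 in total.

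This matches the article. Power with 73 per arm is 80.3%. The calculation is the same whether the rates describe 12-month status or recovery at any visit, so it does not show which definition was planned for.

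**3. Illustration: an effect present at 6 months only**

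Assumptions, not in the article: 35% vs 15% robust at t2; 15% vs 15% at t3; a latent normal variable for each visit with correlation ρ. Only the two scheduled post-baseline visits are used.

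P(robust at either visit) = P(t2) + P(t3) − P(both), with P(both) from the bivariate normal distribution.

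| ρ | Control | Intervention | RR |
|---|---|---|---|
| 0.5 | 0.15 + 0.15 − 0.058 = 0.242 | 0.35 + 0.15 − 0.100 = 0.400 | 1.65 |
| 0.7 | 0.15 + 0.15 − 0.078 = 0.222 | 0.35 + 0.15 − 0.123 = 0.377 | 1.70 |

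The chance of a significant result is 0.49 (ρ = 0.5) to 0.50 (ρ = 0.7) with 66 per arm, and 0.53 to 0.54 with 73 per arm. The lower number is 95 × 0.70 = 66.5, rounded down, which applies the stated 30% attrition to the recruited 95. The true 12-month RR in this scenario is 1.0.

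**4. The same question without a correlation model**

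Again assume 15% robust at 12 months in both arms. Add 20 points of recovery lost by 12 months in the intervention arm, and vary that amount in controls.

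| Lost recovery in controls | Robust at any visit | RR | NNT | Power, 73 per arm |
|---|---|---|---|---|
| 0 points | 35% vs 15% | 0.35/0.15 = 2.33 | 1/0.20 = 5 | 80% |
| 5 points | 35% vs 20% | 0.35/0.20 = 1.75 | 1/0.15 = 6.7 | 53% |
| 10 points | 35% vs 25% | 0.35/0.25 = 1.40 | 1/0.10 = 10 | 26% |

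Transient recovery in controls shrinks the contrast, so the direction of the distortion is not fixed.

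**5. Why the horizon of the planning rates matters**

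If 15% and 35% are 12-month rates, naming t3 leaves the sample size unchanged. Suppose instead that they are rates of recovery at any visit, that the control rate at 12 months is still 15%, and that only part of the 20-point excess persists. Power at 12 months with 73 per arm is then:

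| Share of excess kept | 12-month rates | Power |
|---|---|---|
| 100% | 35% vs 15% | 80.3% |
| 75% | 30% vs 15% | 58.5% |
| 50% | 25% vs 15% | 32.5% |
| 25% | 20% vs 15% | 12.2% |

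**The case against.** - **The rule does not literally say at any time.** This is correct. The abstract compares reversal at each time point and then gives the same effect measures, and Analysis strategy compares frailty status with baseline at each point. The event could therefore mean transition from baseline to a given visit, with 12 months as the main one. That reading is possible, but no sentence states it, and the section that defines the primary event points the other way. What stands is that counting recovery at any visit is the natural reading, not the stated text.
- **The hierarchy already exists.** This is also correct. The abstract's aim and the Aims section both name 12 months, and the earlier points are secondary. This limits how freely a definition could be chosen later. It also makes the mismatch plain, because the event rule admits what the Aims make secondary.
- **Fading would be visible.** A reader might infer that a short-lived effect would be presented as lasting reversal. The article does not say so, and the planned comparisons by time point could reveal fading. The primary RR and NNT would not.
- **The planning rates.** A reader might also infer that the rule cuts the link to 15% and 35%. That is not shown: the rates carry no horizon and their wording fits either definition. The link is unspecified, not broken.
- **The size is hypothetical.** The correlations and the complete loss of effect by 12 months are assumptions, and nothing in the article predicts them. The figures show what the rule permits, not what is expected.

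**Conclusion.** The point holds as a mismatch between aim and event definition. The main aim is fixed at 12 months post-intervention. The main-analysis rule names no visit and requires no persistence, and nothing elsewhere in the article ties the event to t3. Followed as written, the primary RR and NNT can count patients who have relapsed by 12 months.

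Under the stated assumptions (correlation 0.5 to 0.7, effect at 6 months only), the rule gives about 38-40% vs 22-24%, RR 1.65 to 1.70, and significance about half the time with 66 to 73 per arm, with no true 12-month difference. If the effect persists and few patients change status between visits, the two definitions come close together. If controls recover transiently, the rule can understate the contrast.

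This should be settled before analysis, because it determines which question the trial's headline result answers.

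**What to change.** 1. In Main analysis of effectiveness, replace the period at the end of the event definition with a visit: the single primary event is 0 Fried criteria at t3, 12 months post-intervention. Compute the primary accumulated incidence, RR and NNT on that event.
2. Give the main outcome in Study variables the same time point, and mark 12 months as primary where the abstract (Methods) and Analysis strategy list the time points.
3. Keep earlier Fried status secondary, as the Aims section already does, and report robust-at-any-visit as exploratory only.
4. In Sample size, state that 15% and 35% refer to 12 months, or give their actual horizon. If they are not 12-month rates, restate the power for the 12-month event.

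The cost is wording. Fried criteria at t3 are already scheduled in Table 1, so no data are added, and the sample size is unchanged if the planning rates are 12-month rates.

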### Inclusion criteria

Following the 2014 Consensus Document on the prevention of frailty and falls in the elderly patient [29] we will recruit individuals > 70 years of age, with a Barthel test score ≥ 90 and meeting at least one of the following two criteria: a score between 9 and 11 in the short physical performance battery (SPPB) [30] or FRAIL questionnaire with values 1 or 2 [31, 32]. At baseline (t1), pre-frail patients will be included (1 or 2 frailty criteria according to Fried: unintentional weight loss, exhaustion, weakness, slowness, and low physical activity) [4].

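### The stated primary comparison is valid but does not use the baseline Fried count (1 or 2); prespecifying adjustment for it is a small, nearly costless gain in precision

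*Protocol article*

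**What the plan says.** All references are to the protocol article.

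- **Main analysis of effectiveness.** The event is the "transition from pre-frailty (1 or 2 Fried criteria) to robust status (zero Fried criteria) during the study period". The result is reported as "The accumulated incidence in each group, the relative risk (RR), the number-needed-to-treat (NNT) will be calculated, with their corresponding 95% confidence intervals". No model, stratum or covariate is mentioned, and both starting counts are pooled in the event.
- **Inclusion criteria.** "At baseline (t1), pre-frail patients will be included (1 or 2 frailty criteria according to Fried". The count is therefore an entry condition and is known for every patient.
- **Randomization.** "Patients will be randomized into IG or CG after completion of baseline data collection (t1". The process is automated in the electronic notebook, and no stratification factor is named. Table 1, however, shows the allocation column ahead of the t1 baseline column.
- **Analysis strategy.** "A baseline comparison will be made between the groups: in terms of descriptive, outcome, and prognostic variables". The next sentence reads "The appropriate bivariate statistical tests will be used according to type of variable (qualitative or quantitative".

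**The concern.** A patient who starts with one criterion becomes robust by losing it, while a patient who starts with two must lose both. The starting count is thus part of how the outcome is defined and is its most obvious candidate predictor. It is collected on everyone and costs nothing more to use. An estimate taken straight from the two arm incidences leaves the variation explained by the count in the error term.

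The only use the article states for prognostic variables is the between-arm baseline comparison, apparently by significance tests. After randomisation those tests examine a null hypothesis that is true by design, and they neither prevent nor correct a chance imbalance. At stake are a modest amount of precision and a clear prior statement of what will be adjusted for.

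**Working it through.** **1. Reproduce the plan's sample size.** Sample size section: 15% versus 35%, alpha 0.05, power 80%. Sidedness is not stated; two-sided is assumed because it reproduces the plan's figure. With pooled variance under the null:

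n = [1.96 × √(2 × 0.25 × 0.75) + 0.8416 × √(0.15 × 0.85 + 0.35 × 0.65)]² / 0.20² = (1.2002 + 0.5014)² / 0.04 = 72.4, so 73 per arm and 146 in total. This matches. Power at 73 per arm is Φ[(0.20 × √73 − 1.2002) / 0.5958] = Φ(0.854) = 80.3%.

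**2. Assumptions needed.** The documents do not give the share starting with one criterion or how strongly the count predicts reversal. Assumed: share 50 to 70%; odds ratio for reversal (one versus two) from 1 to 4, the same in both arms; overall rates held at 15% and 35%.

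**3. Variance after adjustment, one case in full.** Share 60%, odds ratio 3. The implied reversal rates for one/two criteria are 19.9%/7.6% (control) and 44.3%/21.0% (intervention).

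- Crude n × Var(RD) = 0.1275 + 0.2275 = 0.355.
- Within-count variance = 0.6 × (0.199 × 0.801 + 0.443 × 0.557) + 0.4 × (0.076 × 0.924 + 0.210 × 0.790) = 0.3381.
- The risk difference is 24.4 points with one criterion and 13.4 with two. Standardising over the pooled mix adds ½ × 0.6 × 0.4 × 0.110² = 0.0015.
- Ratio = 0.3396 / 0.355 = 0.957. The effective n is 73 / 0.957 = 76.3 per arm, and power is 82.0%.

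**4. Over the assumed range (73 per arm, risk-difference scale).**

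| Odds ratio | Variance reduction, RD | Variance reduction, log RR | Power |
|---|---|---|---|
| 1 | 0% | 0% | 80.3% |
| 2 | 1.5–2.1% | 1.3–1.7% | 80.9–81.2% |
| 3 | 3.4–4.9% | 2.7–4.1% | 81.7–82.3% |
| 4 | 4.9–7.5% | 3.9–6.2% | 82.3–83.3% |

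**5. Check by simulation.** Crude two-proportion test against the Mantel-Haenszel test, 40,000 runs per setting, 73 per arm.

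- Share 60%, constant odds ratio: 80.9 vs 81.6% (odds ratio 2), 80.7 vs 82.3% (3), 80.6 vs 83.1% (4).
- Share 55%, common RR of 35/15, control rates for one/two criteria of 20%/9% (control odds ratio 0.25/0.099 = 2.5): 81.0 vs 82.8%. At 22%/6% (0.282/0.064 = 4.4): 80.2 vs 84.0%.
- Count not prognostic: 80.8 vs 80.7%.
- Type I error was about 5% for both tests.

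**6. Size of a chance imbalance.** At a 60% share, the between-arm difference in the share starting with one criterion has SD √(2 × 0.6 × 0.4 / 73) = 8.1 points. A 2-SD imbalance with an assumed prognostic gap of 20 points moves the crude risk difference by 2 × 0.081 × 0.20 = 3.2 points. The standard error of that risk difference is √(0.355/73) = 7.0 points.

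**7. Sparse cell.** At a 55% share, about 73 × 0.45 = 33 control patients start with two criteria. At 9% or 6% reversal, that is about 3 or 2 events. The cell is empty in about 5% or 14% of simulated trials.

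**The case against.** The strongest objection is that nothing in the stated analysis is wrong. A relative risk taken from arm incidences is valid in a randomised trial and matches the two-proportion basis of the sample size. Chance imbalance is random error that the confidence interval already covers; the 3.2-point shift in step 6 is under half a standard error. The article never calls the RR crude and does not rule out adjustment. Covariates are commonly left to a statistical analysis plan, which is not shown. All of this stands, and it limits the point to an improvement on the stated method.

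Three stronger readings are tempting, and the documents support none of them.

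- *The unadjusted RR is biased or wrong.* Randomisation rules this out.
- *The gain is large.* A gain to about 88 or 89% power needs control rates such as 25%/3%, an odds ratio of 0.333/0.031 = 10.8. No figure in the article supports that.
- *Adjustment is needed because power is below 80%.* At 73 per arm the crude power is 80.3%. A shortfall arises only from the attrition allowance: 190 is 146 × 1.3, and losing 30% of 190 leaves 133, with power 76.5%. That is a separate matter, and for odds ratios of 2 to 4 adjustment would bring it only to 77.2–79.7%.

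On the baseline tests, the sentence about bivariate tests follows the baseline comparison but could be meant generally. No primary result depends on it.

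**Conclusion.** The point holds as a modest efficiency improvement. The plan leaves unused a covariate that is an entry condition and is built into the outcome. Under assumed odds ratios of 2 to about 4, using it is worth roughly 1 to 4 power points at 73 per arm. With a non-prognostic count there is no gain and essentially no loss. These figures rest on an assumed one/two mix and an assumed prognostic strength, so they show a plausible range and are not a prediction for this trial.

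The case for age and sex as further covariates is not made by anything examined here. The baseline tests are a reporting matter. The conflict in order between Table 1 and the Randomization section should be settled because it decides whether the t1 count is plainly a pre-randomisation covariate.

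**What to change.** - Prespecify the primary RR adjusted for baseline Fried count (1 versus 2) only. Name one method in advance: Mantel-Haenszel, or a Poisson model with log link and robust variance.
- Obtain the risk difference and NNT by standardising over the pooled baseline mix, so that they remain marginal quantities as the article intends. Keep the crude 2x2 table as a supportive result.
- Describe baseline characteristics by arm without significance tests.
- Reconcile Table 1 with the Randomization section, so that it is clear the count is recorded before allocation.

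The cost is about one paragraph of text and no new data. The downside is that the primary estimate becomes stratified or model-based, with few events among control patients who start with two criteria (about 2 to 3 in the cases above). The chosen method should therefore be stated together with how an empty cell will be handled.
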